## Definitions

Withdrawal: Patients died or were discharged early due to non-respiratory causes (e.g., infectious shock, cardiac insufficiency, new congenital anomalies discovered after inclusion in the study, family wishes, etc.). All withdrawn patients need to record the specific reason for withdrawal.

Lost to follow-up: Difficult to follow-up after discharge due to family wishes or loss of contact information.

Discontinuation: Patients requiring higher respiratory support/ECMO due to difficulty maintaining oxygenation with the ventilator parameters established by protocol; all patients discontinuing the study should be evaluated by the attending, and the specific reasons and ventilator parameters should be documented by the investigator.

Adverse events/side effects: adverse events that may be caused by the intervention, such as air-leak syndrome, ventilator-associated pneumonia (VAP), and unplanned extubation. We will report all adverse events. If patient diagnosed with air-leak syndrome after enrollment, we will evaluate placing a chest tube depend on the hospital protocol. If unplanned extubation happened, we will evaluate patient’s respiratory condition to decide whether reintubate or not. If an adverse event such as unplanned extubation or pneumothorax occurs leading to early termination of the patient from the study, we will report the percentage of occurrence.

All predictable adverse events and adverse events need to be listed in the informed consent form and explain to the family. Unpredictable adverse events/adverse events need to be communicated to the family promptly after they occur and consent to continue the study. The occurrence of adverse events/adverse reactions needs to be judged by the attending whether to continue the current study and documented by the investigators to discuss whether the cause of occurrence is due to the study protocol for subsequent improvement.

Partially predictable adverse events are listed in the secondary outcomes.

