### Exclusion criteria

Infants with the following exclusion criteria will not be eligible to participate:Fatal congenital malformations or chromosome abnormality found before or after randomization, orDiaphragmatic hernia, meconium aspiration syndrome, and air leak syndrome, orHigh-frequency oscillatory ventilation (HFOV) or any other invasive mode has been used before, orRefusal to participate in the trial.

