### Primary outcome

Death or BPD at 36 weeks’ postmenstrual age will be used as the primary outcome. BPD will be diagnosed by clinical physicians. The definition and diagnostic criteria of BPD is according to NIH 2018 [16]. We have chosen “death or BPD (36w)” as our primary outcome to maintain similarity with previous trial comparing VTV and PCV [10].

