### Statistical methods

All efficacy analysis will be conducted on an intention-to-treat basis. The SPSS version 26.0 (SPSS, Chicago, IL) software will be used for statistical analysis. Clinical characteristics of infants will be described as mean with standard deviation or median with range for continuous variables and rate or percentage for categorical variables. Absolute risk differences with 95% confidence intervals (CIs) between VTV and PCV will be calculated for binary outcomes, and odds ratios with 95% CIs will be estimated by univariate logistic regression, followed by multivariate logistic regression if the prespecified baseline characteristics are unbalanced between the two groups. Absolute mean differences with 95% CIs (using *t*-test) or mean differences with P25-P75 (using Hodges-Lehmann) will be also calculated for continuous outcomes, and adjusted differences will be estimated by multivariate liner regression if needed. A *P* value < 0.05 was considered statistically significant.

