### Methods in analysis to handle protocol non‐adherence and any statistical methods to handle missing data

Patients with missing outcome data will be censored at last contact. Descriptive statistics on the use of non-protocolized modes as well as intolerance of conventional ventilation mode (duration in days and percentage of time in study spent on HFOV) will be provided.

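### Non-respiratory deaths are defined as withdrawals and some infants are excluded after randomisation, so infants with a primary event can leave an analysis described as intention-to-treat

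*Protocol article*

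**What the plan says.** - **Primary outcome:** death or BPD at 36 weeks' "postmenstrual age will be used as the primary outcome". Death is not restricted by cause.
- **Statistical methods:** "All efficacy analysis will be conducted on an intention-to-treat basis". Binary outcomes are analysed by risk difference and logistic regression.
- **Definitions, withdrawal:** "Withdrawal: Patients died or were discharged early due to non-respiratory causes". The examples include infectious shock, cardiac insufficiency, newly found congenital anomalies and family wishes. The only stated consequence is that the reason be recorded.
- **Exclusion criteria:** "Fatal congenital malformations or chromosome abnormality found before or after randomization".
- **Sample size:** 31 per group, raised to 68 in total because 20% of patients may withdraw.
- **Definitions, discontinuation:** "Discontinuation: Patients requiring higher respiratory support/ECMO due to difficulty maintaining oxygenation with the ventilator parameters established by protocol", followed by "all patients discontinuing the study should be evaluated by the attending". For adverse events such as unplanned extubation or pneumothorax "leading to early termination of the patient from the study, we will report the percentage of occurrence".
- **Sections pointing the other way on rescued infants:** failure of conventional ventilation and use of HFOV as rescue are secondary outcomes. Data collection speaks of discontinuing or deviating from the intervention protocol. The section on non-adherence and missing data will report the "percentage of time in study spent on HFOV".

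**The concern.** A death is itself a primary event. An infant who dies of septic shock before 36 weeks has reached the endpoint, yet the Definitions section files that infant with those who went home early or whose family declined to continue. An infant whose fatal anomaly is found after randomisation becomes ineligible in retrospect. Intention-to-treat requires both infants to stay in their randomised arm with their outcome counted. If instead they are removed, the comparison is made among infants selected by something that happened, or was discovered, after randomisation. With about 34 infants per arm, a few such infants can move the result.

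A secondary problem is that the article gives two accounts of infants who need more support than the protocol settings allow. One phrase has them leaving the study; three other sections imply that they remain in it. These infants are plausibly at high risk of the primary outcome, so their status should not be left open.

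**Working it through.** **1. The plan's own figure.** Inputs from Sample size: 26% (VTV) vs 64% (PCV), two-sided 0.05, 90% power. The unpooled normal approximation gives

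n = (1.960 + 1.282)² × [0.26 × 0.74 + 0.64 × 0.36] / 0.38² = 10.51 × 0.4228 / 0.1444 = 30.8, so 31 per group, or 62 in total.

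This reproduces. The total of 68 exceeds 62 by 6, and 6/68 = 8.8%. An increase above 62 to allow for withdrawal makes sense only if withdrawn infants contribute no outcome. That is the one indication in the article of how withdrawals are treated. (That 68 does not supply a 20% allowance on 62 is a separate matter.)

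**2. The rules side by side.**

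| Infant | Primary outcome and intention-to-treat | Definitions, Exclusion criteria, Sample size |
|---|---|---|
| Dies of a non-respiratory cause before 36 weeks | Event, counted | Withdrawal; withdrawals are sized as lost |
| Fatal anomaly found after randomisation | Counted as randomised | Excluded |
| Needs higher support | Counted as randomised | Described as discontinuing the study, but other sections imply still in it |

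No sentence returns the first two kinds of infant to the analysis. The missing-data rule, censoring at last contact, does not do so either: a risk difference or logistic regression for a binary endpoint has no censored category.

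**3. Size if non-respiratory deaths are dropped.** Let p be the true event rate in an arm and m the proportion of that arm who die of non-respiratory causes. All of these are events, so the rate among those left is (p − m)/(1 − m). The values of m, and the 45% used below, are assumptions.

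*No true effect, 45% in both arms:*

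| m in the two arms | Rates after dropping | False difference |
|---|---|---|
| 10% vs 10% | 0.35/0.90 = 38.9% in both | 0 |
| 10% vs 5% | 0.35/0.90 = 38.9% vs 0.40/0.95 = 42.1% | 3.2 points |
| 15% vs 5% | 0.30/0.85 = 35.3% vs 0.40/0.95 = 42.1% | 6.8 points |

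The arm with more non-respiratory deaths looks better. In the last row, starting from 34 per arm, 28.9 and 32.3 infants remain on average. The standard error is √(0.353 × 0.647/28.9 + 0.421 × 0.579/32.3) = 0.124, and the chance of a significant result is about 8.5% instead of 5% (normal approximation).

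*Planned effect, 26% vs 64%, with m = 10% in both arms:* 0.16/0.90 = 17.8% vs 0.54/0.90 = 60.0%. The difference grows from 38 to 42.2 points. With equal m it is 0.38/(1 − m), so 40 points at 5% and 47.5 at 20%. Equal loss therefore does no harm when there is no effect, but exaggerates an effect that exists.

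**The case against.** The strongest reply is that the Definitions section only labels what happened to an infant. It defines no analysis set, while Statistical methods states intention-to-treat outright. On that reading a withdrawn infant who died would still be an event, and the wording is merely untidy. This limits the claim: the article does not say that these infants will be removed, and it nowhere says they will be scored as non-events. It does not dispose of the claim, because the exclusion criterion does act after randomisation, the sample size treats withdrawals as lost, and nothing says that withdrawn infants are counted.

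Some stronger readings are tempting but not supported:

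- *Rescued infants leave the study.* One phrase in Definitions suggests it. Against it stand HFOV rescue as a secondary outcome, the link in Data collection between discontinuing and the intervention protocol, and the reporting of time in study on HFOV. This is a conflict to reconcile, not a settled rule of removal.
- *Unblinded attending physicians decide which deaths are non-respiratory.* Attending physicians are unblinded and evaluate discontinuations and continuation after adverse events, but no section says who judges cause of death or whether a malformation is fatal.
- *The exclusion and the withdrawal definition describe the same anomaly.* They overlap. The exclusion concerns fatal malformations and chromosome abnormalities; the withdrawal definition lists newly found congenital anomalies, not only fatal ones, as a reason for death or early discharge.
- *About 14 infants (20% of 68 = 13.6) with events could vanish.* The 20% is an allowance for all withdrawals, including early discharge and family wishes.

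It is also fair to say that a fatal anomaly predates randomisation and cannot be caused by the ventilation mode. That supports a sensitivity analysis without those infants, not their removal from the primary one.

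**Conclusion.** Wrong as written. The withdrawal definition and the exclusion after randomisation conflict with a cause-unrestricted primary outcome and with intention-to-treat. Following the stated rules can take primary events out of the primary analysis. The wording on infants needing higher support contradicts other sections and must be reconciled with them.

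The size is illustrative only, since the documents give no non-respiratory death rate: 0 to about 7 points of false difference in the cases shown, and about 4 points of exaggeration under the planned effect if 10% of each arm is dropped. The unequal cases rest on a strong assumption. Holding both arms at 45% while non-respiratory deaths differ by 15% vs 5% forces the remaining events to be 30% vs 40% of those randomised, an opposing 10-point difference. They show how the distortion arises; they do not forecast it.

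**What to change.** 1. Remove death from the withdrawal definition, and state that death from any cause before 36 weeks' postmenstrual age is a primary event.
2. State that discontinuation means leaving the assigned mode only, with outcome follow-up continuing to 36 weeks, and bring the passage on early termination after adverse events into line. This concerns follow-up and analysis; it changes no rule on when support is escalated or a mode is stopped.
3. Delete the words extending the exclusion to findings after randomisation. Keep every randomised infant in the primary analysis, and report the set without fatal anomalies as a sensitivity analysis.

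**Cost.** A protocol amendment. In-hospital deaths should already be in the clinical record. Outcomes are collected before discharge and the trial ends when the last infant is discharged or dies, so infants discharged before 36 weeks may need a follow-up contact. Counting deaths unrelated to ventilation dilutes the treatment difference slightly.

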### Sample size

An RCT of VLBW infants with respiratory distress syndrome(RDS) receiving VTV or PCV as their primary respiratory support mode showed that the BPD/death rate of 26% and 64% respectively [15]. Based on this study, a sample size of 31 in each group will have 90% power to detect statistically difference at a 0.05 tow-sided significance level (MedSci, Shanghai, China). Considering a 20% of patients may withdraw from the research, a sample size of 68 will be appropriate.

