## Data collection and management

### Data collection

Data will be collected on a web-based electronic case record form by research investigators. Some collected data can be obtained from the clinical records, and the rest will be collected from the ventilator at the bedside. Clinical information will be collected in three forms at the following times: demographic information will be collected at trial entry, baseline information will be collected after randomization, and outcome information: including primary outcomes, secondary outcomes, and others. Outcomes will be collected before discharge. And other observational information like ABG, ventilator settings, and respiratory mechanics will be collected 1 h after using the ventilator and same time each day until extubation.

Any participants who discontinue or deviated from the intervention protocol has to collect the specific reason.

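### The Definitions section describes infants who fail the assigned mode or have an adverse event as leaving the study, which conflicts with the rest of the protocol; it should say they leave the assigned mode

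*Protocol article*

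**What the plan says.** All of the wording at issue is in the Definitions section of the protocol article.

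- **Discontinuation.** The trigger is a need for higher respiratory support or ECMO because oxygenation cannot be held within the protocol's ventilator settings. The entry goes on: "all patients discontinuing the study should be evaluated by the attending", with reasons and ventilator parameters documented.
- **Adverse events, reporting.** A percentage is promised for events such as unplanned extubation or pneumothorax "leading to early termination of the patient from the study".
- **Adverse events, decision.** The occurrence of an adverse event "needs to be judged by the attending whether to continue the current study".

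Other sections describe the same infants differently.

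- **Data collection:** "Any participants who discontinue or deviated from the intervention protocol has to collect the specific reason". What is discontinued here is the intervention protocol.
- **Statistical methods:** "All efficacy analysis will be conducted on an intention-to-treat basis".
- **The section on non-adherence and missing data** promises descriptive statistics that include "percentage of time in study spent on HFOV". It also states: "Patients with missing outcome data will be censored at last contact".
- **Secondary outcome** lists failure of conventional ventilation, rescue HFOV and air leak syndrome as outcomes to be measured.

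**The concern.** Definitions is where bedside staff would look to learn what discontinuation means, and there it means leaving the study. The infants concerned cannot be managed on the assigned mode or have had an event such as a pneumothorax. They are likely to be at high risk of death or BPD at 36 weeks' postmenstrual age, which is the primary outcome.

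The attending physician who judges continuation is not blinded (blinding section). Failure of conventional ventilation can also be declared on the clinical team's view alone (Secondary outcome, criterion iv). If staff took the wording at face value and stopped collecting outcomes, the loss would be related to the outcome and could differ by arm. If they took it to mean leaving the ventilation mode, nothing would be lost. The text should allow only the second reading.

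**Working it through.** **Comparison of the text**

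1. An infant moved to HFOV because the protocol settings no longer hold oxygenation meets the Discontinuation entry and is there described as discontinuing the study. The non-adherence section counts that infant's HFOV days as time in study. Both cannot be true, and this is the clearest conflict.
2. Intention to treat needs the 36-week status of every randomised infant in the assigned group. Study exit on need for escalation works against that.
3. Data collection ties discontinuation to the intervention protocol; Definitions ties it to the study. One term has two meanings.
4. Rescue HFOV, failure of conventional ventilation and air leak are secondary outcomes, so they are expected events within the trial. The section on care after extubation likewise returns a reintubated infant to the assigned mode.
5. If an outcome did go missing, the rule is "Patients with missing outcome data will be censored at last contact". Censoring gives no value for a binary outcome at a fixed time that is analysed by risk difference and logistic regression. The rule applies only once an outcome is missing, so it does not itself cause the loss.

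**Scale**

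Inputs from Sample size: "the BPD/death rate of 26% and 64% respectively" for VTV and PCV; 31 per group at 90% power and two-sided 0.05; 68 infants in total. The 1:1 ratio gives 68/2 = 34 per arm.

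The plan's own figure reproduces with the unpooled formula: (1.960 + 1.282)² × (0.26 × 0.74 + 0.64 × 0.36) / 0.38² = 30.8, so 31 per group. The rewording does not affect it.

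Observed rate after one infant with an event is lost: (34p − 1)/33.

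- PCV, p = 0.64: (21.76 − 1)/33 = 62.9%, a fall of 1.1 points.
- VTV, p = 0.26: (8.84 − 1)/33 = 23.8%, a fall of 2.2 points.

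A loss under PCV narrows the observed difference; a loss under VTV widens it.

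**Direction, on assumed figures.** The document gives no discontinuation rate. Suppose a share f of an arm leaves and every one of those infants has the event. The remaining rate is then (p − f)/(1 − f).

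| Assumed loss, VTV / PCV | Observed VTV | Observed PCV | Difference |
|---|---|---|---|
| 0% / 0% | 26.0% | 64.0% | 38.0 points |
| 5% / 20% | 0.21/0.95 = 22.1% | 0.44/0.80 = 55.0% | 32.9 points |
| 10% / 30% | 0.16/0.90 = 17.8% | 0.34/0.70 = 48.6% | 30.8 points |
| 10% / 10% | 0.16/0.90 = 17.8% | 0.54/0.90 = 60.0% | 42.2 points |

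The bias can go either way. These rows show direction only and are not estimates for this trial.

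**The case against.** The strongest reply is that this is loose wording with no consequence. For discontinued infants, Definitions asks only for evaluation and documentation. It lists withdrawal, loss to follow-up and discontinuation as separate categories, and it ties discontinuation to the ventilator parameters, so the mode is the natural subject. Infants on HFOV or ECMO normally remain inpatients, outcomes are collected before discharge partly from clinical records, and the trial runs until the last infant is discharged or dies. A change of support therefore does not make 36-week status unavailable.

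Much of this stands. A reader might infer that the protocol tells staff to stop following these infants, or that the primary result will be biased. The documents support neither. No section stops outcome collection, and the intention-to-treat statement, the data collection wording and the HFOV statistic make continued follow-up the likely intention.

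It does not remove the conflict. Exit from the study is worded three times, no sentence says that discontinued infants are followed to 36 weeks, and the judgement lies with unblinded clinicians. The separate categories are weak protection, because the withdrawal entry itself includes deaths from non-respiratory causes, which are primary-outcome events.

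It may also be said that an article leaves follow-up rules to the full protocol. The point here is that the article makes incompatible statements, not that detail is absent.

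Two cautions on the remedy are right. Families can withdraw, so continued participation cannot be unconditional, and true study exits after an adverse event must still be reported.

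**Conclusion.** The point holds as a conflict of wording that permits avoidable, outcome-related loss of high-risk infants. Loss is a risk and not a consequence that the text dictates. The size of any bias is unknown, because no discontinuation rate is given, and it is zero if the infants are followed. The falls of 1.1 and 2.2 points per lost event rest on the planning rates and an equal split of 68. They would apply to an event lost for any reason, so they show how sensitive a trial of this size is and do not measure this fault. That these infants are at high risk of the primary outcome is a clinical presumption. The change should be made because it is nearly free and leaves only the reading that fits intention to treat.

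**What to change.** Amend the Definitions section as follows.

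1. In the Discontinuation entry, make the subject *all patients discontinuing the assigned mode*. Add: *Unless the family withdraws consent for data collection, the infant remains in the study; death or BPD at 36 weeks' postmenstrual age is collected and analysed in the assigned group.*
2. In the adverse-event reporting sentence, replace "leading to early termination of the patient from the study" and the reporting clause after it with: *leading to early termination of the assigned mode, or to withdrawal of consent by the family, we will report the percentage of each*. True study exits are then still counted.
3. In the sentence on the attending's judgement, have the attending judge *whether to continue the assigned mode*.

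Leave unchanged the request for the family's agreement to go on after an unpredictable adverse event, since that properly concerns participation.

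**Cost.** A formal amendment to the ethics committee, as the Protocol amendments section requires. No new visit, data field or sample size is needed. The trial status section reports that recruitment has begun, so the 36-week status of any infant already treated as having left the study should be checked and recovered where possible.

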## Trials status

Version number: 3, 2023 March 01.

This trial started recruiting patient since 2023 May 01. Sixty-eight infants will be recruited over 1 year. The trial will terminate when the last recruited infant is discharged from the hospital or dies.

